### Sample size and power considerations

The sample size calculation is based on the detection of a minimal clinical important difference between groups on six points on the FACT-P questionnaire [28] at 12 weeks with a standard deviation of 15 FACT\_P points. A two-sided significance level of 5 % and power of 80 % were chosen; The standard deviation is based on a previous exercise trial [30] but increased slightly as FCPC participants will be more heterogeneous than the participants in that trial. Consequently, 100 participants will be needed in each group, i.e. 200 participants in total, in order to detect a statistically significant difference between groups. No interim analysis will be performed. However, if the

anticipated sample size has not been enrolled by 1 May 2017, recruitment will end and final analyses will be performed with the number of patients recruited at that point.

### Randomisation

*Sequence generation*, the allocation of participants, will be done using a computer-generated list of random numbers. The allocation will be stratified by center and by androgen deprivation status (yes/no) with a 1:1 allocation using random block sizes. A statistician not involved in the trial uploaded all the allocation sequences in the trial management system. The eligibility

[figure not shown]

[figure not shown]

**Fig. 3** Assumed causal pathways

of participants will be assessed by either investigators or project nurses at each center. The randomisation will be performed centrally by researchers at the University Hospitals Centre for Health Research, Copenhagen University Hospital, Rigshospitalet.

*Allocation concealment* will be implemented, as the allocation sequence will be hidden from the researchers and, using web-based trial management, no one other than the statistician who uploads the random number lists have access to the lists.

**Table 3** Outcomes with specified measurement variable, analysis metric, method of aggregation and time point

| Concept                         | Specific measurement variable                                       | Patient- level analysis metric | Method of aggregation | Time point(s)       |
|---------------------------------|---------------------------------------------------------------------|--------------------------------|-----------------------|---------------------|
| Primary outcome                 |                                                                     |                                |                       |                     |
| Quality of life                 | Functional Assessment of Cancer Therapy - Prostate Questionnaire    | Change from baseline           | Mean                  | 12 week             |
| Secondary outcomes              |                                                                     |                                |                       |                     |
| Quality of life                 | Functional Assessment of Cancer Therapy - Prostate Questionnaire    | Change from baseline           | Mean                  | 6 month             |
| Muscle mass                     | Whole-body lean body mass                                           | Change from baseline           | Mean                  | 6 month             |
| Fat mass                        | Whole-body fat mass                                                 | Change from baseline           | Mean                  | 6 month             |
| Whole body bone strength        | Whole-body bone mineral content                                     | Change from baseline           | Mean percent          | 6 month             |
|                                 | Whole-body bone mineral density                                     | Change from baseline           | Mean percent          | 6 month             |
| Self-reported physical activity | International Physical Activity Questionnaire                       | Change from baseline           | Mean                  | 12 week and 6 month |
| Functional well-being           | Subscale from Functional Assessment of Cancer Therapy-Questionnaire | Change from baseline           | Mean                  | 12 week and 6 month |
| Regional bone strength          | Lumbar spine bone mineral density                                   | Change from baseline           | Mean percent          | 6 month             |
|                                 | Femoral neck bone mineral density                                   | Change from baseline           | Mean percent          | 6 month             |
|                                 | Total hip bone mineral density                                      | Change from baseline           | Mean percent          | 6 month             |
| Safety                          | Participants with any fracture                                      | Number in each group           | Proportion            | 6 month             |
|                                 | Participants with falls that resulted in seeking medical assessment | Number in each group           | Proportion            | 6 month             |
| Exploratory outcomes            |                                                                     |                                |                       |                     |
| Dyadic adjustment               | DAS-7                                                               | Change from baseline           | Median                | 12 week and 6 month |

## Blinding

Lean body mass, fat mass, bone mineral density and bone mineral content outcomes measured with dual-energy X-ray absorptiometry (DXA) at six months will be performed by an external assessor blinded to group allocation. It is not possible to blind participants or staff due to the nature of the intervention.

The analyses will be performed with the group identity blinded and the groups denoted as A and B. Blinded analyses of both the primary and secondary outcomes will be presented to the research group and decisions on the abstract and the conclusion for the main publication will be made before revealing group identity.

## Data collection

A web-based trial data management system (easytrial.net) will be used to collect data on the primary outcome, FACT-P and the other self-reported outcomes (International Physical Activity Questionnaire (IPAQ), seven-item Dyadic Adjustment Scale, SF-12 and EQ-5D-5 L), in addition to demographic characteristics at baseline. The web-based trial data system will distribute questionnaires and invitations to DXA scans according to the date for randomisation. The trial data system will send a unique e-mail to each trial participant's personal e-mail address. Applied to both groups, this procedure will ensure that responses are unaffected by an interviewer or changing conditions. Participants will be asked to complete questionnaires 12 weeks and six months after randomisation, and come to a six-month DXA assessment, even if they discontinue the allocated treatment. Non-adherence to the allocated intervention is thus not necessary off study, and participants will still be encouraged to do follow-up assessments.

DXA scans will be used to collect data on body composition: LBM and fat mass, and bone markers: bone mineral content (BMC) and bone mineral density (BMD). Data accuracy will be ensured, as participants will add questionnaire responses directly into the trial data system, while DXA outcomes extracted from DXA scanners will also be directly added into the trial data system. The trial data system adheres to the International Council for Harmonisation Guideline on Good Clinical Practice (ICH-GCP) and the Danish data protection legislation. Figure 1 provides time points for data collection, study visits, enrolment, intervention and assessments.

## Statistical methods

### Plan for statistical analyses

The primary statistical analysis targets the effect on PCA specific QoL of a treatment policy offering community-based football to men with PCA. In particular, patients will be analysed in the treatment group to which they were randomly allocated according to the intention-to-

treat principle. The appropriate method for addressing this effect will depend on the assumptions made about missing data (dropouts). Our main analysis is valid under the missing at random assumption but we will also present sensitivity analyses robust to non-ignorable patterns among patients with incomplete data.

Per protocol analyses will be performed to estimate the de jure effect of the treatment for compliant patients. The per protocol population will be defined as intervention group participants who attended the football intervention at least 12 times in the first 12 weeks and 24 times in the six-month intervention period.

Significance tests will be two-sided with a maximal type I error risk of 5 %. To address the problem of multiple comparisons for secondary analyses when several outcomes are tested or multiple constructs are extracted from the same statistical model, p-values will be adjusted using the step-down Bonferroni method of Holm [31] or appropriate modern alternatives.

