## Abstract

**Background:** Prostate cancer is the most common non-cutaneous malignancy in men. Today most patients may expect to live years following the diagnosis and may thus experience significant morbidity due to disease progression and treatment toxicity. In order to address some of these problems exercise has been suggested and previously studies have shown improvements of disease specific quality of life and a reduction in treatment-related toxicity. Cohort studies with long term follow up have suggested that physical activity is associated with improved survival in prostate cancer patients. Previously one randomised controlled trial has examined the efficacy of football in prostate cancer patients undergoing androgen deprivation therapy to usual care and reported positive effects on lean body mass and bone markers. Against this background, we wish to examine the effectiveness of community-based football for men diagnosed with prostate cancer.

**Methods:** Using a randomised controlled parallel group, multicenter, superiority trial design, two hundred prostate cancer patients will be recruited and randomised (1:1) to either community-based football one hour twice weekly or to a control group. The intervention period will be six months. The primary outcome is quality of life assessed after 12 weeks based on the change from baseline in the Functional Assessment of Cancer Therapy–Prostate questionnaire. Secondary outcomes are change from baseline to six months in quality of life, lean body mass, fat mass, whole body and regional bone markers, as well as physical activity and functional capacity at 12 weeks and six months. Safety outcome variables will be falls resulting in seeking medical assessment and fractures during the six-month period.

**Discussion:** Football is viewed as a case for non-professional, supervised community-based team sport for promoting long-term physical activity in men diagnosed with prostate cancer. This randomised trial will provide data on effectiveness and safety for men with prostate cancer when football training is delivered in local football clubs.

**Trial registration:** Clinicaltrials.gov identifier: NCT02430792

**Keywords:** Prostate cancer, Soccer, Exercise, Physical activity, Quality of life

\* Correspondence: [contact]

University Hospitals Centre for Health Research (UCSF), Rigshospitalet, University of Copenhagen, Copenhagen, Denmark

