### The football intervention

Participants allocated to the intervention group will be offered one hour of recreational football twice weekly. The football training sessions consist of a 20-min warm-up based on the FIFA11+ concept, though modified to suit older players [27]. Next, participants will spend 20 min practising dribbling, passing and shooting. The training sessions will then end with 20 min of 5–7-a-side football. Two coaches recruited from the local football club will be in charge of all training sessions. The coaches are expected to have experience as either a player or coach but no other formal qualifications are required. The coaches will be required to have passed a first-aid course and to complete a 10-h course involving lectures on PCa treatment, patient experiences of PCa and a manual describing the content of the training, including the FIFA 11+ concept intended to prevent injuries. Participants will be told to avoid hard tackles and other actions that carry a risk of injury. In the event of injuries participants will remain in their allocated group and will be encouraged to participate in football practice again after recovery. Adherence to the intervention will be recorded by the coaches. Participants

allocated to football training will be able to track their individual adherence and compare it to an average adherence rate of participants in the football group. A logical model, presented in Table 2, summarises the key inputs, activities and intended outputs of the intervention, while Fig. 2 presents the activities and Fig. 3 shows the assumed causal pathways for the effect of the intervention on the individual.

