### Outcomes

The *primary outcome* is change in PCa-specific QoL from baseline to 12 weeks measured with the fourth version of the Functional Assessment of Cancer Therapy–Prostate (FACT-P) questionnaire [28], a self-reported, multidimensional QoL instrument specific for PCa patients [29]. The questionnaire consists of 27 general cancer items covering four domains - physical, social/family, emotional and functional well-being - supplemented with 12 specific PCa-related items. All items are scored on a 0–4 Likert scale. The total FACT-P score ranges from 0 to 156, higher scores indicating higher QoL.

Table 3 presents all outcomes with specified measurement variable, analysis metric, method of aggregation and time point.

The 12-Item Short Form Health Survey (SF-12) and EQ-5D-5 L, a standardised instrument by EuroQol for use as a measure of health outcome, will be collected for use in later economic evaluations of the intervention.

[figure not shown]**Fig. 1** Trial design and timeline

**Table 2** Logic model: The FCPC Trial

| Inputs (resources)                                                                                                                                                                                                                                                                                                                                                                                                                                                      | Activities                                                                                                                                                                                                                                                                                                                                                         | Outputs                                                                                                                                                    | Outcomes (short-term)                                                                                                                                                                                                                                                 | Impacts (long term)                                                                                                                                                                                           |

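### The per-protocol set filters the football arm only and, as worded, uses attendance after week 12, so it cannot deliver the *de jure* effect it is said to estimate

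*Protocol*

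**What the plan says.** The Protocol's primary analysis is by intention to treat. Beside it, under Plan for statistical analyses, stands a second one: "Per protocol analyses will be performed to estimate the de jure effect of the treatment for compliant patients". The population for it is fixed in the next sentence: it is "defined as intervention group participants who attended the football intervention at least 12 times in the first 12 weeks and 24 times" over the six months. The whole attendance rule reads "at least 12 times in the first 12 weeks and 24 times in the six-month intervention period".

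Four other places bear on this:

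- **Outcomes:** the primary outcome is "change in PCa-specific QoL from baseline to 12 weeks".
- **The football intervention:** men in that arm "will be offered one hour of recreational football twice weekly", and their attendance is recorded by the coaches.
- **Control group:** controls get a short telephone session and e-mailed activity guidelines. No compliance measure is described for them.
- **Blinding:** "The analyses will be performed with the group identity blinded and the groups denoted as A and B". Blinded results for the primary and secondary outcomes go to the research group before group identity is revealed.

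**The concern.** Three features of the definition matter, in falling order of weight.

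1. **The filter acts on one arm.** Football men who attend little are removed. Controls who would have attended little cannot be identified, so they stay. Attendance is plausibly tied to health and motivation, and FACT-P covers physical and functional well-being. A difference between the two sets then mixes any effect of football with the kind of man who keeps coming. That mixture is not the effect in compliant patients.
2. **One rule covers two time points.** The thresholds are joined by *and*. Taken literally, a man's place in the 12-week analysis depends partly on what he did in months four to six, after the outcome was measured. How he felt at week 12 may influence that later attendance.
3. **Masking.** A filter that shrinks only one of groups A and B could show which one is football.

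At stake is the reading of a supportive result. A per-protocol gain presented as the effect of actually playing could be given causal weight that it has not earned.

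**Working it through.** **The plan's own figure.** Difference 6, SD 15, two-sided 5 %, power 80 % (Sample size and power considerations): n = 2 × (1.96 + 0.84)² × 15² / 6² ≈ 98.1 per group by the normal formula and 99.1 with the t correction, rounded up to 100. Power at 100 per group is 80.7 %. The stated 100 per group is reproduced and is not in dispute.

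**Thresholds against the schedule.** Two sessions a week give 24 in 12 weeks and about 52 in 26 weeks ("The intervention period will be six months"). The thresholds are 12/24 = 50 % and 24/52 = 46 % of sessions offered. Under the joint rule, a man with 12 to 23 sessions by week 12 still needs 24 minus that number, i.e. 1 to 12 later sessions. Only a man who attended all 24 qualifies on week-12 data alone.

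**Bias from the one-arm filter.** Assumptions, none from the Protocol: no true effect; a share f of football men meets the rule; would-be attenders change by g points more than the others, equally in both arms; comparator all 100 controls; no covariates.

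- Mean of attenders minus mean of all controls = (1 − f) × g.
- SE = √(225/(100f) + 225/100).
- False-positive rate = Φ(b/SE − 1.96) + Φ(−b/SE − 1.96), where b is the bias.

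| f | g | Bias b | SE | False-positive rate |
|---|---|---|---|---|
| 0.8 | 3 | 0.6 | 2.25 | about 6 % |
| 0.6 | 6 | 2.4 | 2.45 | about 16 % (0.165) |
| 0.5 | 6 | 3.0 | 2.60 | about 21 % |

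The central bias is 2.4/6 = 40 % of the planned difference. Simulating that case (100 per arm) gave means of about 0.0 for intention to treat and 2.4 for per protocol.

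**A second model of the same bias.** Let attendance propensity correlate ρ with FACT-P change, and keep the top share f of football men. The bias is 15 × ρ × φ(c)/f, where φ is the normal density and c the cut-off that leaves share f. For ρ from 0.1 to 0.3 and f from 0.8 to 0.5, the bias runs from 0.5 to 3.6 points and the false-positive rate from 5.6 % to 29.1 %.

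**The joint rule alone.** Assumptions: individual attendance probability Beta(2.5, 2); change unrelated to early attendance; no effect; 10, 20 or 30 % stop after week 12 at average change, with the log-odds of stopping 0.5 lower per SD of better change. The joint rule then drops 14, 24 or 33 % of men who met the 12-week threshold. The mean change among those kept is 0.8, 1.4 or 2.2 points. Under a 12-week-only rule it is about 0, as it must be when early attendance is unrelated to change.

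**The case against.** Several points on the other side stand.

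- **The size is assumed.** The Protocol gives neither an attendance rate nor an attender gap, and the central gap was set equal to the full 6-point difference. The calculation omits baseline score, age and ADT. If the per-protocol analysis uses the primary model, part of the bias goes, by an unknown amount.
- **The comparator is inferred.** The Protocol never says which controls enter. Read literally, the set contains none. All controls is the only workable choice, since nothing is recorded on which controls could be filtered.
- **The *and* has a benign reading.** Two thresholds and two assessment times suggest that 12 sessions may have been meant for 12-week outcomes and 24 for six-month outcomes. The text does not say so, and an SAP that is not at hand may settle it.
- **Masking is only a possible conflict.** The Blinding section does not say whether per-protocol analyses are run before the code is broken.
- **The complier estimate is not bias-free.** Its mean near zero in the null simulation is guaranteed, because nobody benefits there. Suppose compliers (60 %) gain 6 points and partial attenders (40 %) gain 3. Intention to treat is then 0.6 × 6 + 0.4 × 3 = 4.8, and the complier estimate is 4.8/0.6 = 8.0, which is 2.0 too high.

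A reader might infer that this analysis would show a benefit even if football did nothing. The documents do not support that. In the central assumed case the test is falsely significant about 16 % of the time instead of 5 %. That is an inflated error rate, not an assured positive result. Lack of participant blinding is a separate matter that touches the intention-to-treat analysis too, and it forms no part of these figures.

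None of this rescues the mismatch between a one-arm filter and the stated target. The Protocol itself fixes both, so this is more than a detail left open.

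**Conclusion.** The point holds in limited form. A filter on the football arm alone does not estimate the effect in compliant patients unless attendance is unrelated to how men would have fared anyway, given the covariates. Under the stated assumptions and without adjustment, the bias is 0.6 to 3.0 points against a planned difference of 6, with 2.4 points in the central case. Its direction favours football only if attenders would have done better regardless.

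The one-sided filter is certain from the text. The dependence of 12-week membership on later attendance is certain only on the literal reading. The masking problem is a possibility.

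The consequence is confined to the supportive per-protocol analysis. The intention-to-treat primary analysis, its error control and the sample size are not affected.

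**What to change.** 1. **Thresholds.** State that at least 12 sessions by week 12 defines compliance for 12-week outcomes only, and at least 24 sessions by six months for six-month outcomes only. This costs one sentence.
2. **Estimate or label.** Choose one:
   - Estimate a complier-average effect with randomisation as the instrument, keeping all randomised men in both arms and the same covariates. State that it assumes no benefit below the threshold and overstates the effect if partial attenders benefit. It costs one extra model and some precision: at 60 % compliance the simulated SD of the estimate is 3.7 points, against 2.5 for the filtered comparison.
   - Or keep the filtered comparison, name all controls as the comparator, drop the *de jure* label, and report it as non-randomised and supportive.
3. **Timing.** Run the per-protocol analysis after the A/B code is broken and the main conclusions are fixed. This costs nothing beyond sequencing.

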### Secondary outcomes including safety outcomes

Changes from baseline to six months for LBM, BMD, BMC and total body fat mass will be analysed in the same manner as the primary outcome.

QoL, functional well-being and physical activity (based on metabolic equivalent of task values derived from IPAQ) measured at baseline, 12 weeks and six months will be analysed using a mixed model for repeated

measurements. Changes from baseline to 12 weeks or six months will be treated as the response. The model will include fixed effects of factors: group, ADT, sampling time and their interactions, and the analysis will be adjusted for age and baseline value. The correlation between measurements on the same participant will be modelled using a random effect of participant.

Safety outcomes will be listed for each group and the number of falls that resulted in seeking medical assessment and fractures will be compared across groups using Fisher's exact test.

Subgroup analyses will be reported for the patients treated with ADT, which means that results will be given for both the overall treatment effect and for the subgroup obtained by stratifying according to ADT. To verify the credibility of our subgroup analyses, we will apply the criteria proposed by Sun and colleagues [33], i.e. the subgroup variable is a baseline characteristic, a stratification factor, specified a priori and includes only a small number of analyses.

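### Followed as written, the plan puts the two safety tests (fractures, medically assessed falls) in the multiplicity-adjusted secondary family; safety should be a separate, unadjusted category

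*Protocol*

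**What the plan says.** Three places in the protocol bear on the point.

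- **Plan for statistical analyses.** All tests share one level: "Significance tests will be two-sided with a maximal type I error risk of 5" per cent. The adjustment rule follows: "To address the problem of multiple comparisons for secondary analyses when several outcomes are tested", or when several constructs come from one model, p-values are adjusted by Holm's step-down method or a suitable modern alternative. No outcome is exempted, and neither the members nor the size of the family is given.
- **Table 3.** Its group headings are primary, secondary and exploratory. The rows for any fracture and for "Participants with falls that resulted in seeking medical assessment" carry the label Safety, but they stand under the secondary heading, before the exploratory one.
- **The analysis section headed** "Secondary outcomes including safety outcomes". It provides for listing safety events by group and for a between-group comparison by Fisher's exact test.

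Other text sets safety somewhat apart. The abstract and the Objective section each give safety its own sentence, and the outline of figures and tables gives it its own table. The same outline leaves safety out of the figure of primary and secondary outcomes by naming it as an exception, which is needed only if safety counts among them.

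**The concern.** Familywise adjustment guards against claiming a benefit because many outcomes were tested. For a harm outcome the costly error is usually the opposite one, missing a real excess, and adjustment makes that error more likely. Here the bar for showing harm would also rise with each efficacy outcome added to the family, which has nothing to do with the safety question.

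Safety is a stated objective of the trial, and the abstract promises data on it. Under the Blinding section, analyses of primary and secondary outcomes are shown to the research group as groups A and B, and the conclusion is settled before the groups are identified. At that stage the significance label may carry weight. If the label is an adjusted one, a sizeable imbalance could be described as not significant.

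**Working it through.** **1. The plan's own figure.** Inputs from the sample size section: a "minimal clinical important difference between groups on six points on the FACT-P questionnaire", an SD of 15, two-sided 5% and 80% power. Then n per arm = 2(1.960 + 0.842)² × 15²/6² ≈ 98.1, rounded up to 99. The protocol states "100 participants will be needed in each group, i.e. 200 participants in total", so its figure is reproduced. I use 100 per arm below.

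**2. Size of the family, counted from Table 3** (outcome by time point, secondary heading only):

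| Outcome | Tests |
|---|---|
| FACT-P at 6 months | 1 |
| Lean mass | 1 |
| Fat mass | 1 |
| Whole-body BMC and BMD | 2 |
| IPAQ, two times | 2 |
| Functional well-being, two times | 2 |
| Regional BMD, three sites | 3 |
| **Efficacy subtotal** | **12** |
| Fractures and falls | 2 |
| **Total** | **14** |

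**3. Threshold.** Holm compares the smallest of m p-values with 0.05/m. After k rejections the next is compared with 0.05/(m − k). At the first step with m = 14 this is 0.05/14 = 0.0036. After six rejections it is 0.05/8 = 0.00625.

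**4. Smallest significant excess** (two-sided Fisher, 100 per arm, exact enumeration):

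| Level | Control 0 | Control 1 | Control 2 | Control 5 |
|---|---|---|---|---|
| 0.05 (unadjusted) | 6 | 8 | 10 | 15 |
| 0.025 (safety as its own two-test family) | 7 | 9 | 11 | 16 |
| 0.05/14 (first step of 14) | 9 | 12 | 14 | 20 |

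With no control events, 6 vs 0 gives p = 0.029 and 9 vs 0 gives p = 0.0032. In between, 8 vs 0 gives p = 0.0068; multiplied by 14 this is 0.095. Families of 12 or 13 tests give almost the same thresholds as 14.

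**5. Power to flag an excess in the football group.** The protocol gives no event rates, so these are assumptions spanning rare to common events:

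| Football vs control | Unadjusted | Two-test family | First step of 14 |
|---|---|---|---|
| 5% vs 1% | 19% | 11% | 2.5% |
| 10% vs 2% | 59% | 46% | 21% |
| 12% vs 3% | 61% | 49% | 23% |
| 20% vs 5% | 88% | 82% | 57% |

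At a later step, after six other rejections (0.05/8), power at 12% vs 3% is 30%, and 9 vs 0 is still needed.

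**6. Effect on efficacy.** Removing the two safety tests changes the first efficacy step from 0.05/14 = 0.0036 to 0.05/12 = 0.0042, a small gain.

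**The case against.** The best counter-argument is that the adjustment of safety is inferred. No sentence says that the Fisher p-values are Holm-adjusted or that all secondary rows of Table 3 form one family. The abstract, the objectives and the separate safety table suggest that the authors may have thought of safety as distinct. The plan also allows alternatives to Holm, and family membership is often left to a statistical analysis plan, which is not at hand here. This stands in part: the 14-test family and the 0.0036 threshold are conditional, and 0.0036 applies only while the safety p-value is the smallest. It does not remove the point. The protocol itself classes safety as secondary and itself states a rule for secondary analyses without exception, so an analyst who followed it literally would adjust.

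It is also fair that listing by group keeps the raw counts in view, and that for rare events the test misses most real excesses even without adjustment: 19% power at 5% vs 1%. Both stand.

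A reader might infer that the plan expressly subjects safety to a 14-test correction, or that harm would be hidden. The documents support neither. The first rests on reading three passages together, and the second is contradicted by the promised listing and table. What remains is a possible misleading label on visible data.

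**Conclusion.** The point holds in a conditional form. On its plain reading the protocol includes the two safety tests in the adjusted secondary family, without saying so outright. If the family is all 14 secondary tests and the safety p-value is the smallest, the excess needed with no control events rises from 6 to 9 men per 100. Power then falls by about a third (88% to 57%) to nearly nine-tenths (19% to 2.5%) over the assumed risks. With safety as a two-test family the loss is much smaller (7 vs 0; 61% to 49% at 12% vs 3%). Removing the adjustment eases the problem but does not give the trial good power for rare harms, so a non-significant result would be weak reassurance either way. The change is worth making because it is simple and removes a real ambiguity, but it does not threaten the primary analysis.

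**What to change.** - **Table 3 and the secondary-outcome analysis section:** make safety a category of its own, outside the secondary outcomes.
- **Plan for statistical analyses:** state that Holm, or its alternative, covers only the secondary efficacy tests (12 by the count above), and list them.
- **Reporting:** for each safety outcome give the number of participants with at least one event in each group, an unadjusted two-sided Fisher p-value, and the risk difference with an exact 95% confidence interval. Counting participants follows Table 3; the analysis text speaks of numbers of falls and fractures, which a Fisher test on participants cannot use directly.
- **Interpretation:** state that a non-significant safety comparison will not be taken as evidence of safety.

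This costs wording only, with no extra patients, data or time. The downside is a slightly higher chance of flagging a chance imbalance in harm: two tests at 5% have a combined false-alarm probability of at most 1 − 0.95² = 9.75% if independent, and Fisher's test is conservative at low event counts.
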